### Data collection and management

5.3

To evaluate the effect of AA, data will be collected at baseline, upon completion of the intervention, and at short-term follow-up (days 3 and 7 after acupuncture). The data items and the corresponding timeline are summarized in Table 1. A case report form (CRF) has been designed to include the variables of interest. To increase the objectiveness of subsequent statistical analysis, the information obtained by CRF will be transcribed to an electronic database by 2 independent researchers; any disagreement will be solved by discussion. To protect confidentiality of participants, initials will be recorded in CRFs, and all CRFs will be stored in a locked cabinet in Shanghai University of Traditional Chinese Medicine, and will have a unique identification number. The access to the database will be restricted to the researchers in this study team.

**Table 1 T1:**

The schedule of follow-up.

## Statistical methods

6

### Sample size calculation

6.1

A repeated measures design was employed for sample size calculation with GLIMMPSE software (URL: *http://glimmpse.samplesizeshop.org/*) based on the study design and the results of our previous clinical trial.^[35]^ Pain will be measured on a VAS 8 times per patient. When a two-tailed test with a significance level of 5% and a test power of 90% was applied, the number of participants required per group was 26. Therefore, a target sample size of 90 participants is required, assuming a 15% dropout rate. Each group will include 30 initial participants.

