### Primary outcome measures

5.1

The primary outcome will be pain intensity on a VAS,^[30]^ with the primary endpoint at 0 minutes (immediately after treatment). The secondary time point will be at 2 hours after acupuncture treatment, and an area-under-curve analysis will be performed, including baseline, 15 minutes, 30 minutes, 3 days, and 7 days. We chose VAS because it is commonly used to measure pain intensity.^[31]^ The patients will be guided to mark a point on a 0 to 100 mm VAS, in which 100 (at the right end) indicates maximum pain and 0 (at the left end) indicates absolutely no pain.

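### The stated 90% power belongs to a repeated measures design with 8 readings and is not shown to apply to the primary comparison at 0 minutes

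*Protocol article*

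**What the plan says.** Section 6.1 (Sample size calculation): "A repeated measures design was employed for sample size calculation with GLIMMPSE software", drawing on an earlier trial by the same team. It adds "Pain will be measured on a VAS 8 times per patient". The result, for a two-sided test, reads: "a significance level of 5% and a test power of 90% was applied, the number of participants required per group was 26". This is raised to 30 per group, "assuming a 15% dropout rate".

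Section 5.1 (Primary outcome measures) takes pain on the VAS as the primary outcome, "with the primary endpoint at 0 minutes (immediately after treatment"). The 2-hour reading is a secondary time point, and the other readings enter an area-under-curve analysis.

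Section 6.2 (Statistical analysis) plans a repeated measures ANOVA over time and group, followed by Fisher's LSD comparisons of the treatments at each time point. The Discussion (section 7) sets the aim of showing more improvement with AA than in the control patients, and says that the two control groups will establish specificity. No section gives the power for AA against either control at 0 minutes.

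**The concern.** The sample size and the primary endpoint refer to different hypotheses. A repeated measures test of group, or of group by time, draws on all 8 readings. The primary endpoint is one of them, and the questions asked of it are two pairwise contrasts. Power for the first does not carry over to the second without further assumptions.

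At stake is how the result is read. A reader will take 90% as the power of the primary comparison. If AA against sham or against TNM is not significant at 0 minutes, that figure invites the conclusion that a worthwhile effect has been ruled out, although no such power has been shown.

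**Working it through.** **Inputs.** From section 6.1: two-sided α = 0.05, power 0.90, n = 26 per group before dropout, 8 readings, 15% dropout. From section 3.4: three arms, 1:1:1. From section 5.1: primary time point 0 minutes. Not stated: the hypothesis tested, mean difference, SD and within-patient correlation ρ.

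**The plan's own figure.** Without those four inputs, 26 cannot be reproduced. Only the dropout step can: 26 × 1.15 = 29.9, which gives the stated 30, while 26/0.85 = 30.6. With 30 enrolled, 30 × 0.85 = 25.5 remain, half a patient short of 26, which is immaterial.

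**Step 1: what 26 per arm gives at one time point, with no undisclosed input.** Two-sample noncentral t, 50 degrees of freedom, noncentrality d × √(26/2), where d is the difference in SD units.

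- 90% power at 5% needs d = 0.917. Normal approximation: (1.960 + 1.282)/√13 = 0.899.
- 90% power at 2.5%, if α were split over the two contrasts, needs d = 1.00.
- At 5%, power is 81% at d = 0.8 and 42% at d = 0.5.

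**Step 2: power at 0 minutes if the trial was sized on a repeated measures hypothesis.** Assumptions: equal correlation ρ between any two readings; AA differs by d from two equal controls at k of the 8 readings, including 0 minutes; no difference at baseline. k = 7 is an effect lasting to day 7. k = 5 is a same-day effect (8 readings less baseline, day 3 and day 7).

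*(a) Target: group main effect.* The F test on patient means (2 and 75 df) has 90% power at noncentrality 13.17. With one arm differing by D, noncentrality is 26 × (2/3) × D², so D = √(13.17/17.33) = 0.872 SD of the patient mean. That SD is √((1 + 7ρ)/8) of a single reading's SD, so d = 0.872 × √((1 + 7ρ)/8) × 8/k. Example, ρ = 0.5 and k = 7: 0.872 × 0.75 × 8/7 = 0.747.

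*(b) Target: group by time.* The univariate F test (14 and 525 df) has 90% power at noncentrality of about 23.5, which equals 26 × (2/3) × d² × k(8 − k)/8 ÷ (1 − ρ). Example, ρ = 0.8 and k = 5: d = √(23.5 × 0.2/(17.33 × 1.875)) = 0.38.

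Each d then goes into the Step 1 test. Unadjusted pairwise power at 0 minutes:

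| Assumed target and effect pattern | ρ = 0.3 | 0.5 | 0.7 | 0.8 |
|---|---|---|---|---|
| Main effect, sustained (k = 7) | 59% | 75% | 86% | 89% |
| Main effect, same day (k = 5) | 87% | 96% | 99% | 99% |
| Group by time, sustained (k = 7) | 96% | 88% | 68% | 50% |
| Group by time, same day (k = 5) | 71% | 57% | 38% | 27% |

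**Step 3: effect of baseline adjustment.** Adjustment multiplies the residual SD by √(1 − ρ²), ignoring the degree of freedom spent. The difference detectable with 90% power becomes 0.917 × √0.75 = 0.79 SD at ρ = 0.5 and 0.917 × √0.51 = 0.65 SD at ρ = 0.7. Under group-by-time sizing with a sustained effect, adjusted power at 0 minutes is 97%, 95%, 93% and 90% for ρ = 0.3, 0.5, 0.7 and 0.9 (residual variance pooled over three arms). With a same-day effect adjustment does not restore it: at ρ = 0.8, d = 0.381/√(1 − 0.64) = 0.635, and power is about 61%.

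**The case against.** A reader might infer that the trial lacks its stated power for the primary endpoint. The documents do not support that. Section 6.1 does not say which hypothesis was powered, and the table has cells above 90% as well as far below. The Discussion expects sudden relief over several hours, followed by a separate later phase. If the effect is mainly same-day and the trial was sized on the group main effect, averaging over all readings dilutes the effect, and the 0-minute comparison has 87% to 99% power. Lower figures for main-effect sizing (48% to 80% over the same correlations) arise only if the full group difference is placed at baseline too, where randomisation makes the expected difference zero. This objection stands.

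It is also true that sections 6.1 and 6.2 agree with each other, since both use repeated measures, and that an article may leave the numerical inputs to the full protocol and the cited earlier trial. So neither an arithmetic error nor missing inputs is the point. The 90% may be correct for the hypothesis it was computed for.

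A reader might also count seven time points in section 5.1 against eight in section 6.1. The schedule table and figure are not shown and may hold the eighth, so nothing follows from the count.

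What the objection does not remove is the gap between section 5.1 and section 6.1. The article itself fixes one time point as primary and attaches its power claim to a different design.

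**Conclusion.** The point holds in a limited form: 90% power is not established for AA against sham or AA against TNM at 0 minutes. For the same effect, power there runs from about 27% to over 95%, depending on the undisclosed hypothesis, on how long the effect lasts and on the correlation (0.3 to 0.8 assumed, equal between all readings). A shortfall is possible, not shown. The firm figures need none of these assumptions: with 26 per arm, an unadjusted pairwise two-sided 5% test has 90% power only at about 0.92 SD, 81% at 0.8 SD and 42% at 0.5 SD.

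**What to change.** Keep 90 patients. Name the primary comparison as baseline-adjusted VAS at 0 minutes, AA against sham and AA against TNM, and state its power or detectable difference in section 6.1. Example: with 26 per arm and two-sided 5%, 90% power for about 0.79 SD if the correlation with baseline is 0.5, or about 0.65 SD if it is 0.7. Both correlations are assumed and should be replaced by the value from the earlier trial. State which hypothesis the existing calculation addressed, and label its 90% as applying to that repeated measures hypothesis only; it need not be deleted.

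The cost is one recalculation and some wording. The baseline VAS is already collected and no patients are added. The drawback is that the power stated for the primary comparison may be less favourable than 90%.

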### Randomization/allocation

3.4

Only those participants who have signed informed consent and go through the screening will be assigned randomly to one of the three interventions in a ratio of 1:1:1. Randomization number will be generated using a computerized number generator through the stratified block randomization method of the Statistical Analysis System (SAS) package (V.9.1.3; SAS Institute Inc., Cary, North Carolina) by a researcher not involved in this trial. The random numbers will be stored in sealed envelopes for random allocation until an investigator opens each envelope closely before intervention.

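### Thirty enrolled per group does not leave the required 26 after the stated 15% dropout: it leaves 25.5 on average, and covers dropout only up to about 13%

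*Protocol article*

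**What the plan says.** All the figures stand in section 6.1 (Sample size calculation) of the protocol article. The calculation used a repeated measures design: "Pain will be measured on a VAS 8 times per patient". The error rates are given as "When a two-tailed test with a significance level of 5% and a test power of 90% was applied", and the result is that "the number of participants required per group was 26". The article continues: "Therefore, a target sample size of 90 participants is required, assuming a 15% dropout rate", and then "Each group will include 30 initial participants".

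Section 3.4 confirms equal allocation, with participants "assigned randomly to one of the three interventions in a ratio of 1:1:1". The abstract repeats 30 per group and section 3.3 repeats the total of 90, so the enrolment figure is not a misprint in one place. Nothing elsewhere defines the 15% differently or lowers the required 26.

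**The concern.** The article presents 90 as following from two inputs, 26 evaluable per group and 15% dropout. A dropout rate is a fraction of those enrolled, so enrolment has to be the evaluable number divided by one minus the rate. Multiplying the evaluable number by one plus the rate always gives too few. The figure of 30 looks like the result of that shortcut.

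What is at stake is whether the sample size justification is right. The three figures are meant to show that the planned 90% power survives the expected losses. As written, the stated enrolment does not retain the stated requirement at the stated dropout. The introduction faults the existing evidence for lacking appropriately powered trials, so the article's own power statement should add up.

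**Working it through.** **Inputs (section 6.1, with 1:1:1 allocation from section 3.4)**

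- Required per group: n = 26, so 3 × 26 = 78 in total.
- Dropout: d = 0.15.
- Enrolled: 30 per group, 90 in total.

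**1. Reproducing the stated 30**

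n × (1 + d) = 26 × 1.15 = 29.9, rounded up to 30 per group and 90 in total. This matches the article.

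**2. What 30 per group leaves at 15% dropout**

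- Per group: 30 × 0.85 = 25.5, below 26.
- In total: 90 × 0.85 = 76.5, below 78.

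**3. Enrolment that retains 26 at 15% dropout**

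- Per group: n / (1 − d) = 26 / 0.85 = 30.59, rounded up to 31, or 3 × 31 = 93 in total. Check: 31 × 0.85 = 26.35.
- Inflating only the total: 78 / 0.85 = 91.8, rounded up to 92, which does not split into three equal groups.

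Both exceed 90, so 90 is too few whichever way the result is rounded up.

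**4. Dropout that 30 per group does cover**

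1 − 26/30 = 4/30 = 13.3%. In whole participants, four losses in a group leave 26, and five (16.7%) leave 25.

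**5. Illustration of the effect on power**

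The figure of 26 cannot be recomputed, because the article gives no effect size, standard deviation or correlation. As an illustration only, assume a two-group comparison of means (normal approximation, two-sided 5%) with exactly 90% power at 26 per group. Then power at n per group is Φ(3.2415 × √(n/26) − 1.960), where 3.2415 = 1.960 + 1.2816.

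| Evaluable per group | Illustrative power |
|---|---|
| 26 | 90.0% |
| 25.5 | 89.4% |
| 25 | 88.9% |

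Under these assumptions the loss is 0.6 points at 25.5 and 1.1 points at 25.

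**The case against.** The strongest reply is that the gap is trivial and its consequence unproven. Most of this stands.

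- **Power.** A reader might infer that the trial will fall short of 90% power. The documents do not show this. The 26 is a whole number. If it is the smallest that reaches 90%, the unrounded requirement lies anywhere above 25 and up to 26. If that requirement is 25.5 or less, an average of 25.5 still meets the target.
- **Size of the power loss.** A reader might take about 89% as the trial's real power. That figure comes from a two-group model calibrated to 90% at 26. The trial's own calculation is a three-arm repeated-measures one with eight pain measurements, so the illustration indicates scale and no more.
- **Cause.** A reader might state as fact that 26 was multiplied by 1.15. The article prints no formula. Truncating 30.59 to 30, or choosing a round 90, would give the same figure. The shortfall does not depend on which of these happened.
- **Exposure to dropout.** The primary endpoint is immediately after a single 20-minute session (section 5.1), where few losses are likely. Most would fall at days 3 and 7. However, section 6.2 analyses pain by repeated measures ANOVA, so late losses could matter, depending on how missing values are handled. Section 6.1 also applies its 15% to the calculation as a whole.

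What the objection does not remove is the arithmetic. The article states all three figures, so this is not detail left to a fuller document, and no analysis plan can make 30 × 0.85 reach 26.

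**Conclusion.** The point holds as a minor error, wrong as written. The stated 26 required, 15% dropout and 30 enrolled per group are inconsistent. The shortfall is half a participant per group on average, or 1.5 in total (76.5 against 78). Enrolment at 15% would need to be 31 per group, or 93 in total, which is 3 more than planned.

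The conclusion takes the 26 as given and reads the 15% as a share of those enrolled, which is how the article's reference to initial participants reads. The effect on power is small and cannot be determined from the article. It is not a threat to the design, and it gives no reason to enlarge the trial.

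**What to change.** Keep 90 participants and replace the 15% claim in section 6.1 with the allowance that 90 supports, for example: *30 participants per group (90 in total) retain the required 26 per group with up to 13% dropout.* Check: 30 × 0.87 = 26.1.

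Do not insert a figure of about 89% power at 15% dropout unless it is recomputed with the inputs of the trial's own repeated-measures calculation.

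The cost is one phrase. Enrolment, design and analysis stay as they are, and the abstract and section 3.3 need no change. The stated dropout allowance becomes slightly less generous.

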### Statistical analysis

6.2

The Statistical Package for the Social Sciences (SPSS version 21.0) will be used for all statistical analyses. Baseline demographic variables and clinical characteristics will be compared across groups using one-way analysis of variance (ANOVA) for continuous variables and Pearson's χ^2^ tests for categorical variables. The differences in pain VAS scores and paresthesia VAS scores between the AA, sham AA, and TNM groups will be analyzed using repeated measures ANOVA with time as a repeated within-subject factor and group as a between-subject factor. Fisher's least significant difference post-hoc test will be used to compare the effects of the treatments at each time point. Sensation of needling and acceptability ratings (AAPR) will be compared across groups using one-way ANOVA. Pearson's χ^2^ tests will be used to examine the differences between groups. All tests will be two-tailed, with the significance level set at 0.05. Per-protocol (PP) analysis and intention-to-treat (ITT) analysis of the results will be conducted.

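### The primary endpoint is pain at 0 minutes, but the stated analysis is an all-time-point repeated measures ANOVA that neither makes the 0-minute contrasts decisive nor adjusts them for baseline VAS

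*Protocol article*

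**What the plan says.** Section 5.1 (Primary outcome measures) takes pain VAS as the primary outcome, "with the primary endpoint at 0 minutes (immediately after treatment". It makes 2 hours a secondary time point and adds an area-under-curve analysis that includes baseline.

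Section 6.2 (Statistical analysis) states that pain and paresthesia VAS scores "will be analyzed using repeated measures ANOVA with time as a repeated within-subject factor and group as a between-subject factor". It continues: "Fisher's least significant difference post-hoc test will be used to compare the effects of the treatments at each time point". On error rates it says only: "All tests will be two-tailed, with the significance level set at 0.05". It does not say whether the group term or the group-by-time term decides success, and it does not single out 0 minutes. Time and group are the only factors named.

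Section 3.4 (Randomization/allocation) uses the SAS "stratified block randomization method" but does not name the strata.

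Section 6.1 (Sample size calculation) says: "A repeated measures design was employed for sample size calculation with GLIMMPSE software". It adds "Pain will be measured on a VAS 8 times per patient" and arrives at 26 per group at 90% power, raised to 30 for dropout.

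**The concern.** The trial's question is the immediate effect, and one time point has been chosen to answer it. The stated model answers a different question.

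- **Group main effect.** It averages over every time point in the model. That includes days 3 and 7 and, if baseline is a level of time (probable, though section 6.2 does not list the levels), a score that treatment cannot have affected.
- **Group-by-time interaction.** This is an omnibus test. A difference at any time point can make it significant, so a significant result does not identify 0 minutes.
- **LSD at 0 minutes.** This is the comparison that matters, but it stands among all pairs at all time points, with no statement that it is primary. It uses raw post-treatment scores, so stable differences in pain between patients stay in the error term.

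Two things are at stake. One is a clear rule for what counts as a positive result at 0 minutes. The other is precision, which can be gained at almost no cost because baseline VAS is already measured.

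**Working it through.** **Can the plan's own figure be reproduced?** No. Section 6.1 gives no effect size, SD, correlation or tested hypothesis, so 26 per group cannot be rebuilt. For scale, suppose 26 per arm came from a single pairwise comparison at 0 minutes (normal approximation, two-sided 5%, 90% power). The implied standardised effect is d = (1.960 + 1.282) × √(2/26) = 0.90. This is an assumption, not the trial's design value. A smaller effect, d = 0.65, is shown beside it.

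**Effect of baseline adjustment.** With rho the correlation between baseline and 0-minute VAS:

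- residual variance after adjustment = (1 − rho²) × unadjusted variance
- noncentrality = d × √(n/2) / √(1 − rho²), with n = 26 per arm
- unadjusted: 0.90 × √13 = 3.24, and 0.65 × √13 = 2.34

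Power from the noncentral t distribution (two-group comparison, one degree of freedom spent on baseline):

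| rho | 1 − rho² | Power, d = 0.90 | Power, d = 0.65 |
|---|---|---|---|
| unadjusted | 1 | 89% | 63% |
| 0.2 | 0.96 | 90% | 65% |
| 0.3 | 0.91 | 92% | 67% |
| 0.5 | 0.75 | 96% | 76% |
| 0.7 | 0.51 | 99% | 90% |

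The unadjusted 89% differs from 90% only because the t distribution replaces the normal approximation (90.1%).

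**Does the unnamed decision rule matter?** A simulation used 3 arms of 26, compound symmetry with rho 0.3 to 0.7, and an effect of d = 0.90 at 0 minutes in the AA arm only. It used the seven time points that section 5.1 names; section 6.1 counts eight. The power to declare AA different from sham at 0 minutes was:

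- LSD with no gate: about 89–90%
- LSD only if group-by-time is significant: 71–90%
- LSD only if the group main effect is significant: 86–90% for a constant effect, 52–75% for one that decays to a tenth by day 7, and 14–25% for one gone by 2 hours
- ANCOVA at 0 minutes: 92–99.5% throughout

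With no gate, the chance of at least one false positive is about 9–10% for the two AA contrasts at 0 minutes. It is about 36–50% over all pairs and six post-treatment times.

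**Sharing alpha.** With Bonferroni over two contrasts at d = 0.90 (normal approximation), n per arm = 2 × (2.241 + 1.282)² / 0.90² = 30.6, so 31 evaluable without adjustment. Multiplying by 1 − rho² gives 27.9 (28) at rho 0.3 and 23.0 (23) at rho 0.5.

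**Strata.** They are not named, so no loss from omitting them can be calculated.

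**The case against.** The strongest defence is that the plan is valid as it stands, and that an article may leave covariates to the full protocol or SAP. Several parts of this hold.

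- A reader might infer that 0 minutes is not tested. It is: LSD at each time point covers it. What is missing is its designation as primary.
- A reader might infer that baseline VAS goes unused. It does not: section 5.1 puts it in the area-under-curve analysis, and it is probably one of the repeated measurements. It is only not used as a covariate.
- A reader might infer that the trial falls short of 90% power. The documents cannot show that. At d = 0.90 the unadjusted comparison has about 89–90%; the 63% belongs to an assumed smaller effect.
- The gain may be small. The 40 mm entry threshold (section 3.1) restricts the baseline range and may lower rho, and at rho 0.2–0.3 the gain is only about 1 to 4 points.
- The low power under main-effect gating depends on the effect fading. The Discussion also describes a later phase of relief, and with a constant effect this gate costs little.
- A power loss from omitting the strata might also be inferred, but nothing in the documents allows it to be sized.

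The appeal to an SAP does not hold. Section 6.2 is not silent: it names the model, its factors and the post-hoc test. An SAP that followed it would carry the mismatch forward.

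**Conclusion.** The mismatch stands. A single-time-point primary endpoint is paired with an all-time-point model, and the 0-minute contrasts are left as unadjusted, undesignated post-hoc tests. The planned comparison is unbiased under randomisation, so the baseline point concerns precision, not validity.

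The direction of the gain is certain for any rho above zero, apart from one degree of freedom. Its size is conditional: at 26 per arm it runs from about 1 to 10 percentage points at d = 0.90 and from about 2 to 27 at d = 0.65, over rho 0.2 to 0.7. Both d and rho are assumed. The strata are a matter of consistency between design and analysis, of unknown size.

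**What to change.** Before unblinding, amend section 6.2 as follows.

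1. Name the AA–sham and AA–TNM differences in pain VAS at 0 minutes as the primary contrasts.
2. Analyse them by ANCOVA on group, baseline VAS and the randomisation strata, or by a mixed model with baseline as a covariate and the same 0-minute contrasts. Report adjusted differences with 95% confidence intervals.
3. State how the two contrasts share alpha.
4. Keep the repeated measures ANOVA as supportive, and treat paresthesia VAS the same way.
5. Restate the power for the 0-minute contrasts, giving the effect size, SD and rho used, and reconcile the eight measurements in section 6.1 with the seven time points in section 5.1.

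The cost is analysis wording and a few degrees of freedom; no new data are needed. The change is not wholly free, because the stated 90% was derived for a repeated measures design and no longer applies directly. If alpha is split, 26 per arm may or may not suffice, depending on rho.

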### AA group

4.1

After sterilizing with 75% ethanol at and around the needling point, a disposable sterile acupuncture needle (0.35 mm × 40 mm; Tianxie Brand, Beijing, China) will be used. The acupuncturist will hold the needle and swiftly insert it into the skin at the target point with a 30° angle to the skin. Then, the needle will be slowly advanced with a 0° angle to the skin until about 3/4 of the needle enters the subcutaneous tissue. The patients will not feel any *deqi* during this process if the AA is performed correctly. Then, the needle will be retained in the subcutaneous tissue for 20 minutes with the needle handle fixed to the skin with an adhesive tape (Fig. 3B and C).

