### Secondary outcome measures

5.2

Given that paresthesia (e.g., numbness and tingling) is the second most common symptom in sciatica,^[32]^ the sensation will be measured as one of the secondary outcomes. Paresthesia intensity will be assessed using a 100-mm VAS, in which “0” indicates the absence of numbness and tingling and “100” indicates unbearable numbness and tingling.

The sensation of needling is one of the significant outcomes on reliability of the operation. The sensation of needling will be assessed using self-report measures after the needle is withdrawn. The participants will be asked to report any *deqi* sensation such as sourness, numbness, heaviness, warmness, and pain, among others.

Acceptability ratings will be obtained using the Abbreviated Acceptability Rating Profile (AAPR).^[33]^ In AARP, higher scores indicate greater acceptability. The reliability and validity of the Chinese version of AAPR are satisfactory.^[34]^

Any additional treatments received by participants will be asked to report at each follow-up.

Any severe adverse events such as bleeding, hematoma, or fainting during the acupuncture process will be observed and dealt with immediately. The needle will be removed once any of the above-mentioned severe events occur.

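### Needling sensation is described as a report of deqi by kind, with no score defined, yet is assigned to one-way ANOVA; sections 5.2 and 6.2 do not fit together

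*Protocol article*

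**What the plan says.** Section 5.2 of the protocol article (Secondary outcome measures) sets out how the variable is obtained: "The sensation of needling will be assessed using self-report measures after the needle is withdrawn". Patients are asked about any deqi "sensation such as sourness, numbness, heaviness, warmness, and pain, among others". That is an open list of kinds, of which a patient could report none, one or several. No range, intensity or total is given. In the same section paresthesia has a 100-mm VAS, and the acceptability profile (AAPR) has a stated score direction.

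Section 5.2 also gives the variable a role: "The sensation of needling is one of the significant outcomes on reliability of the operation". Section 4.1 (AA group) treats deqi as present or absent: patients should feel none "during this process if the AA is performed correctly".

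Section 6.2 (Statistical analysis) then names the test: "Sensation of needling and acceptability ratings (AAPR) will be compared across groups using one-way ANOVA". The next sentence says that Pearson chi-square "tests will be used to examine the differences between groups", without naming a variable. For baseline data the same section divides tests by type of variable, "using one-way analysis of variance (ANOVA) for continuous variables and Pearson's" chi-square for categorical ones. The level is common to all: "All tests will be two-tailed, with the significance level set at 0.05".

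**The concern.** One-way ANOVA needs a quantity whose mean has a meaning. A list of kinds of sensation has none, and a yes/no report has a proportion. The plan does not leave the test open for a later document. It fixes one by name, and that test does not match the variable as section 5.2 describes it. It also departs from the rule that section 6.2 applies to baseline data.

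At stake is the check that ankle acupuncture was delivered without deqi, and how the three arms compare on it. If coding and test are settled only once data are in hand, the p-value for that check may reflect a coding choice. Where few patients report deqi, it may rest on an approximation that fails with so few events.

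**Working it through.** The plan gives no deqi rates and no figure to reproduce. From section 6.1 the group size is 30, so N = 90 in three arms. **All sensation counts below are assumptions**, in the order AA, sham AA, TNM. Three ways of recording the variable are possible.

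**1. Yes/no, coded 0/1.** Let X² be the Pearson chi-square (2 degrees of freedom) and R² = X²/N, which for 0/1 data is the ANOVA between-group share of the sum of squares. With three groups both p-values have closed forms:

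- chi-square: p = exp(−X²/2)
- ANOVA: p = (1 − R²)^((N − 3)/2) = (1 − R²)^43.5

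*Moderate counts, 6, 4 and 14 of 30.* Expected per arm: 24/3 = 8 yes and 22 no. The squared deviations sum to 4 + 16 + 36 = 56.

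- X² = 56/8 + 56/22 = 9.545, so chi-square p = 0.0085.
- R² = 9.545/90 = 0.1061, so ANOVA p = 0.8939^43.5 = 0.0076.

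The conclusion is the same. In 20,000 simulated null trials at each true rate of 5, 10, 20 and 50%, the two tests rejected equally often (0.034, 0.040, 0.048, 0.049) and never disagreed at 0.05.

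*Sparse counts, 0, 0 and 3 of 30.* Expected per arm: 1 yes and 29 no. The squared deviations sum to 1 + 1 + 4 = 6.

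- X² = 6/1 + 6/29 = 6.207, so chi-square p = 0.045.
- R² = 6.207/90 = 0.0690, so ANOVA p = 0.9310^43.5 = 0.045.
- Exact (Fisher-Freeman-Halton): given three reporters in all, the least likely tables are those with all three in one arm. Their probability is 3 × C(30,3)/C(90,3) = 3 × 4,060/117,480 = 0.104.

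So with three reporters in total, a result that ANOVA and chi-square both call significant at 5% arises by chance about 10% of the time.

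**2. Kind of sensation as a number.** Suppose one kind is recorded per patient:

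| Arm | None | Sourness | Numbness | Heaviness | Warmness | Pain |
|---|---|---|---|---|---|---|
| AA | 16 | 3 | 3 | 2 | 2 | 4 |
| Sham AA | 17 | 1 | 1 | 1 | 1 | 9 |
| TNM | 8 | 6 | 6 | 5 | 2 | 3 |

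- Over all 720 ways of numbering the six categories 0 to 5, ANOVA p runs from 0.00024 to 0.98, and 29% of codings fall below 0.05.
- With none fixed at 0 (120 codings), p runs from 0.0005 to 0.67, and 43% fall below 0.05.
- Chi-square on the table gives 0.044 however the columns are labelled. Several expected counts are small (warmness: 5/3 = 1.7 per arm), so that value is approximate, but it does not move with the labels.

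A second assumed table with weaker differences (12, 3, 4, 3, 2, 6; 12, 2, 2, 2, 2, 10; 11, 6, 5, 4, 1, 3; chi-square p = 0.57) gave 0.017 to 1.00 over 720 codings, with 5% below 0.05. With none fixed at 0 it gave 0.13 to 1.00, none below 0.05. The dependence on coding is real, but its practical size varies with the table.

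**3. Intensity score or count of sensations.** ANOVA could then be used, but section 5.2 defines no such score.

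**The case against.** The strongest defence is that the kind of data is inferred. Self-report measures is a loose term, the list of sensations is only illustrative, and pairing the variable with AAPR under ANOVA suggests that a numeric rating may exist. Section 5.3 mentions a case report form that is not shown, and an article may leave scoring to it. This stands as a limit on the claim: one cannot say that the data will be nominal. It does not remove the mismatch, because the text as published describes kinds of sensation and names a test for means.

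The chi-square sentence might have been meant for this variable. It names none, and could as well refer to the success of blinding or to adverse events, both listed in the Abstract. If it was meant for needling sensation, the section names two tests for one outcome and still needs correcting.

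Three stronger readings are tempting, and the documents do not support them:

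- *That the p-value is arbitrary in general.* For a yes/no variable ANOVA and chi-square practically coincide. The problem arises only if kinds are numbered, and a single code per patient would not hold several sensations reported together.
- *That near-zero variance in two arms inflates the error rate of an intensity analysis.* If AA and sham AA sit at zero and a non-negative TNM score varies, the TNM mean is above zero. The null is then false, and there is no type I error to inflate.
- *That unequal variances are built into the design.* This assumes that TNM produces variable deqi. The article does not say so; sections 3.5 and 4.3 describe TNM as needle retention without manipulation.

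The sparse-count point also has a limit. It concerns particular outcomes with very few reporters. Averaged over the simulated null trials, neither test exceeded 5%.

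**Conclusion.** The point holds in a limited form. Section 5.2 describes needling sensation by kind with no score, section 6.2 assigns it by name to ANOVA, and the two must be reconciled. With numbered kinds the p-value depends on the numbering (0.00024 to 0.98 in one assumed table). With a yes/no variable ANOVA does little harm at moderate counts (0.0076 against 0.0085). Both approximate tests can overstate the evidence when few patients report deqi (0.045 against 0.10 for 0, 0 and 3 of 30). Section 4.1 expects no deqi from correctly performed AA, so low counts are plausible at least in that arm. The sizes rest on assumed counts, since the article gives none.

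Severity is minor. This is a secondary check on delivery, and it touches neither the primary pain analysis nor the two aims stated in the Discussion.

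**What to change.** In section 6.2, keep one-way ANOVA for AAPR only. For needling sensation, compare the proportion of patients reporting any deqi sensation across the three arms by the Fisher-Freeman-Halton exact test. Give the AA–sham AA and AA–TNM differences in proportion with 95% confidence intervals, and describe each kind of sensation by arm. State which variables the chi-square sentence covers.

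If the case report form does record a numeric score, name it and its range in section 5.2 instead, so that the variable and its test agree.

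The cost is one or two sentences, with no new data and no change to sample size.
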